#### Secondary objectives

We will again conduct mixed-effects logistic regression to assess whether self-reported disability, empowerment/self-agency-related measure or service satisfaction with inpatient care at discharge (T2) affect readmission over a 12-month follow-up period beginning at discharge after the index admission, respectively. In addition, we will conduct an analysis that adjusts for the same potential covariates as the QoL analyses. We will only analyze patients with data on self-reported disability (T2), empowerment/self-agency-related measure (T2) or service satisfaction (T2) with inpatient care and readmission.

#### Additional objectives

We will also create mixed models with repeated measures to explore the impacts of readmission on changes in QoL, empowerment/self-agency-related measure, and self-reported disability. In this model, we will adjust for sex, age, diagnosis, baseline score at admission (T1) and present psychiatric status at admission (T1). In addition, we will explore other potential factors that influence the changes in patient-reported outcomes using mixed models with repeated measures. In this analysis, we will include at least the following variables: function (PSP score), length of hospital stay, living condition, and utilization of outreach services after discharge. Because the mixed-model method can accommodate missing data, we will use the data from patient-reported measures completed at least twice at the three follow-up assessments (T2–T4), in addition to the assessment at admission (T1).

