**Discussion:**

The present study may produce evidence on how patient-reported experiences at discharge influence readmission and on the influence of readmission on the course of patient-reported outcomes from admission to community living after discharge. The study may contribute to improving care for both patients’ subjective views of their own health conditions and their community lives in an acute psychiatric setting.

*Trial registration* University Hospital Medical Information Network—Clinical Trials Registry (UMIN-CTR) UMIN000034220. Registered on September 20, 2018.

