In terms of the Japanese context, Japan is undergoing a transition from inpatient care to community mental health care. Most psychiatric care is still provided in inpatient settings [36]; the average length of psychiatric hospitalization is approximately 300 days [37]. The Japanese government has reformed relevant laws to prevent long-term inpatient care starting in the 21st century. Clinicians have started to develop systems for community care [37, 38]. These changes have resulted in the fact that more than 80% of inpatients were discharged within 1 year [39]. Nevertheless, approximately 40% of inpatients are rehospitalized within 1 year after discharge [38]. Some recent studies in Japan based on analyses of the national database have noted that highly intensive medical support delivered as part of inpatient care and follow-up visits has potentially reduced the risk of readmission [40, 41]. However, most Japanese empirical studies on psychiatric readmission have focused on the system level. Few studies have comprehensively examined either the individual factors that predict readmission after discharge or patient-reported outcomes after discharge, particularly in acute psychiatric care settings. In other words, both clinical variables and patient-reported measures related to hospitalization and community living in Japan remain unclear.

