## Aims and objectives

To address the evidence gap, we initiated the ePOP-J study (early discharge and Prognostic community Outcomes for Psychiatric inpatients in Japan: a longitudinal study), which is a multicenter prospective cohort study designed to investigate multiple factors, including patient-reported measures, associated with readmission and community living, in acute psychiatric patients in Japan. The overarching aim of the present study is to explore the association between patient-reported experiences and outcomes and the incidence of readmission during 12 months of follow-up. In this study, patient-reported measures, particularly QoL, will be used to assess both exposures and outcomes. The study primarily aims to evaluate the following associations and factors, although we will also perform a comprehensive exploratory analysis to identify other (non-patient-reported) factors for readmission after evaluating the described associations and factors:The relationship between readmission during the 12-month follow-up beginning at discharge after the index admission (primary outcome), and the QoL score at discharge (primary exposure).The association between readmission during the 12-month follow-up beginning at discharge after the index admission and the self-reported disability score, empowerment/self-agency-related measure score or inpatient care service satisfaction score at discharge.Influence of readmission on changes in scores for patient-reported outcome measures (QoL, self-reported disability and empowerment/self-agency-related outcome) during the study period.Other potential factors influencing score changes in patient-reported outcome measures, such as age, sex, diagnosis, length of hospital stay, living conditions, and utilization of outreach services after discharge.

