## Methods and analysis

### Study design and settings

A multicenter prospective cohort study has been planned. The study protocol was designed by professional researchers, clinicians, and mental health services users. Specifically, our project team has involved a mental health service user researcher as a core member, and we collaboratively determined the study participants’ eligibility criteria, recruitment methods, and outcomes and exposures. We employed a prospective design for this study to repeatedly assesses patient-reported experiences and outcomes in situations where these measures are not routinely evaluated in the current mental health care system in Japan. We recruited 21 psychiatric hospitals with acute wards. Because human resources that perform research work vary considerably among psychiatric hospitals in Japan, we needed to recruit only hospitals with sufficient staff members to conduct a prospective study. Therefore, we used a snowball sampling method across Japan instead of using random sampling. The study will assess acute ward inpatients’ exposures and outcomes at admission (T1), discharge (T2), 6 months after discharge from the index admission (T3), and 12 months after discharge from the index admission (T4). We will also evaluate exposures and outcomes among inpatients who cannot be discharged within 12 months of the index admission (Fig. 1). Patient recruitment began on 1 October 2018.

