### Procedures for data collection

After informed consent is obtained, participants will complete a self-administered questionnaire at the time of admission (T1). The staff members will assist by reading the questionnaire if necessary. Trained staff members will also complete the first assessment sheet, which includes sociodemographic information and past medical history, based on medical records. In addition, they will assess staff-rated measures based on observation and a brief interview with the participant. At discharge (T2), the participant will complete the self-administered questionnaire again. Next, staff members will complete staff-rated measures and will document the types of inpatient care that were provided during hospitalization on the second assessment sheet, based on medical records. At 6 months (T3) and 12 months (T4) after the index admission, the participant will complete a self-administered questionnaire, and staff members will complete an assessment sheet detailing staff-rated measures, readmission, and outpatient services. To prevent loss to follow-up at 6 months (T3) and 12 months (T4), staff members in the inpatient care department, outpatient care department, and outreach team will cooperate to share information on each participant’s status.

For participants who are not discharged within 12 months of the index admission, the same procedure used for the discharge survey (T2) will be conducted when the hospital stay reaches 365 days. At this time, the patient’s survey will be concluded. The main analysis will only include participants who are discharged within 12 months.

Data monitoring and management will be conducted by the Department of Community Mental Health and Law, National Center of Neurology and Psychiatry, which is independent from the grant funder. At least two researchers or research assistants will check the data to maintain data quality.

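### Fixed T3 and T4 dates mean some readmitted patients are scored while in hospital, so the pooled readmission effect on patient-reported outcomes does not by itself support a conclusion about community living

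*Protocol article*

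**What the plan says.** **Timing.** Under Study design and settings, the follow-up assessments are "6 months after discharge from the index admission (T3), and 12 months after discharge from the index admission (T4"). Procedures for data collection counts from a different event: "At 6 months (T3) and 12 months (T4) after the index admission, the participant will complete a self-administered questionnaire". The two anchors need to be reconciled, but each gives a fixed date that does not depend on where the patient is.

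**Who is followed.** To limit loss at T3 and T4, "staff members in the inpatient care department, outpatient care department, and outreach team will cooperate to share information" on each participant's status. No rule postpones, excludes or marks an assessment made during a readmission.

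**Objective and model.** The third item under Aims and objectives is "Influence of readmission on changes in scores for patient-reported outcome measures" over the study period. Under Additional objectives the plan is: "We will also create mixed models with repeated measures to explore the impacts of readmission on changes in QoL" and the other two scales. The covariates are then listed: "In this model, we will adjust for sex, age, diagnosis, baseline score at admission (T1) and present psychiatric status at admission (T1"). The list is given as complete, whereas the next model, for other influencing factors, is left open. The article does not say whether readmission is coded as ever/never or by time.

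**Intended reading.** The Abstract's discussion says the study may produce evidence "on the influence of readmission on the course of patient-reported outcomes from admission to community living after discharge". The main Discussion would use factors that influence this course as evidence for improving services in the community.

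**The concern.** A patient who has not been readmitted by T3 or T4 is, by definition, not a psychiatric inpatient on that date. A readmitted patient may be back home or may still be on a ward in a new episode. Assessment in hospital can therefore occur only in the exposed group, and no term in the listed model represents it.

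The protocol accepts that acute state can affect self-report. The section on clinical, social and other measures says so for T1, and the model adjusts for T1 psychiatric status. Table 1 collects that status at T1 only. The one-item symptom rating is collected at T3 and T4 but is not in the readmission model. The limitations in the Discussion do not mention the point.

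What is at stake is interpretation. A lower score among readmitted patients could reflect those on a ward that day, a difference that remains after they go home, or both. These have different implications for community services, and the single readmission term cannot tell them apart. The problem remains at T3 and T4 even if readmission is coded correctly in time.

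**Working it through.** The plan gives no figure for the share of readmitted patients in hospital at T3 or T4, so there is none to reproduce. The check asks how large that share could be.

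**Inputs from the protocol**
- 12-month readmission: about 40% (Background; Sample size consideration).
- Assessment dates: T3 at 182.5 days and T4 at 365 days after index discharge (the anchor in the Abstract and design section).
- Length of a readmission: not given. Two figures lie nearby, and neither is a readmission stay. The Background says "the average length of psychiatric hospitalization is approximately 300 days", a national average. The sample size section assumes 20% not discharged within 12 months, which concerns the index stay; an exponential stay with that property has mean 365/ln 5 = 227 days.

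**Assumptions**
- Mean readmission stay m from 30 to 300 days, exponential, one readmission per patient.
- Two timing patterns: a constant hazard, and a front-loaded pattern with 60% of the year's readmissions uniform over days 0–90 and 40% uniform over days 90–365.

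**Constant hazard.** h = −ln(0.6)/365 = 0.00140 per day. Among those readmitted by day T, the share in hospital at T is

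h (e^(−hT) − e^(−T/m)) / [(1/m − h)(1 − e^(−hT))].

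For m = 60 and T = 365: 0.00140 × (0.600 − 0.002) / (0.01527 × 0.400) = 0.137.

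**Front-loaded, T4.** 0.6 (m/90)(e^(−275/m) − e^(−365/m)) + 0.4 (m/275)(1 − e^(−275/m)). For m = 60: 0.003 + 0.086 = 0.09.

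**Front-loaded, T3.** [0.6 (m/90)(e^(−92.5/m) − e^(−182.5/m)) + 0.4 (m/275)(1 − e^(−92.5/m))] / (0.6 + 0.4 × 92.5/275). For m = 60: (0.067 + 0.069)/0.735 = 0.18.

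| Assumed mean stay (days) | Constant: T3 | Constant: T4 | Front-loaded: T3 | Front-loaded: T4 |
|---|---|---|---|---|
| 30 | 15% | 7% | 7% | 4% |
| 60 | 30% | 14% | 18% | 9% |
| 90 | 41% | 21% | 30% | 14% |
| 227 | 68% | 46% | 60% | 38% |
| 300 | 74% | 55% | 68% | 47% |

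With 40% readmitted, the T4 extremes are 0.40 × 4% = 1.6% and 0.40 × 55% = 22% of all discharged patients.

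The T3 denominator is patients already readmitted by T3. If readmission were coded ever/never over 12 months, the exposed group at T3 would also include patients not yet readmitted. Under the constant hazard the T3 share would then be about 9%, 17%, 23% and 42% for mean stays of 30, 60, 90 and 300 days.

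**Effect on the readmission term.** Pooled difference = share × (inpatient difference) + (1 − share) × (difference once back home). Suppose being an inpatient lowers a score by 0.5 SD and nothing persists (both assumed). The term would still show 0.5 × share: 0.03 to 0.37 SD at T3 and 0.02 to 0.27 SD at T4.

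**The case against.** **The objective does not promise a lasting effect.** The third objective and the model description speak of the influence of readmission on score changes during the study. A total effect that includes time on the ward is a legitimate answer to that. This stands. A reader might infer that the model fails its own objective or that the study sets out to separate temporary from lasting harm. The documents do not support that: the Background's remark that recovery continues through a crisis is conceptual and defines no contrast. The gap lies between the total effect and the community-living reading.

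**It is not shown that many patients will be affected.** This also stands. No readmission stay is given, and the same Background paragraph that gives the 300-day average says more than 80% of inpatients leave within a year. With 30-day stays the T4 share is only 4% to 7%. The shares also assume that inpatients complete the form. The limitations say, for T1, that very severe symptoms can prevent this.

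**The distortion may not be large.** A reader might infer that the pooled effect is several times the lasting one. That multiple follows from the values assumed. At T4 under the constant hazard, with an inpatient deficit of 0.60 SD and a lasting deficit of 0.05 SD, the pooled effect is 0.137 × 0.60 + 0.863 × 0.05 = 0.13 SD for 60-day stays (2.5 times) and 0.55 × 0.60 + 0.45 × 0.05 = 0.35 SD for 300-day stays (7 times). With a lasting deficit of 0.20 SD, the results are 0.25 SD (1.3 times) and 0.42 SD (2.1 times). Nothing in the documents chooses between these. The direction is not given either: the listed states include mania, with no statement of how it moves self-report.

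**It may be settled elsewhere.** The coding of readmission and any sensitivity analyses may sit in an analysis plan that is not shown. That is a fair reason for restraint on coding. The adjustment list, however, is stated here, and it has no term for being in hospital.

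**Conclusion.** The point holds in a limited form. With fixed T3 and T4 dates and the stated covariates, the readmission term is a total effect that mixes current inpatient status with any effect after return home. It answers the third objective as worded, but cannot by itself carry the community-living conclusion in the Abstract and Discussion.

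The size is not known. Among those already readmitted, about 7% to 74% would be in hospital at T3 and 4% to 55% at T4. These ranges rest on assumed mean stays of 30 to 300 days, exponential stays, one readmission per patient and two timing patterns. The upper end uses a national average that is not a readmission figure.

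The primary and secondary logistic regressions, which use T2 scores to predict readmission, are untouched. The model concerned sits under Additional objectives, although the Abstract names the effect of readmission on these outcomes among the questions the study will primarily investigate. The change is worth making because it is cheap and decides what can be said about life after discharge.

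**What to change.** 1. **Determine inpatient status on the T3 and T4 questionnaire dates.** Table 1 lists number of admissions and length of hospitalisation at both points, but not admission or discharge dates. If dates are on the staff assessment sheet, derive the status; if not, add one yes/no item or take it from the medical record.
2. **Keep the overall readmission effect** as the answer to the third objective, labelled as a total effect that includes time in hospital.
3. **Report beside it the same mixed model with a three-state time-varying exposure:** not readmitted to date; readmitted and back in the community; inpatient at assessment. Give the number of patients in each state at T3 and T4.
4. **Base any statement about community living on the split,** not on the pooled effect. If the cells are sparse, a sensitivity analysis limited to scores taken in the community is a fallback.
5. **Reconcile the two anchors for T3 and T4,** since the status has to be dated against one of them.

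The cost is one derived variable or one item, and one further model. There are two statistical downsides. The split contrasts will have wider intervals because the readmitted group is divided. The back-in-the-community contrast also conditions on something that happens after readmission: it leaves out patients still in hospital, who tend to have the longest stays, so it may understate the effect. It should be labelled as conditional on discharge and should not replace the overall effect.

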### Sample size consideration

Based on the primary aim of this study, the sample size was calculated using the effect size reported by a previous study. That study reported an association between readmission and QoL scores (*d* = 0.26) [20] and indicated the readmission rate in Japanese psychiatric hospitals (40%, ratio of approximately 1 vs 1.5) [38]. In addition, the calculation was based on a power of 70% at a two-sided significance level of 5%. Based on these values, 430 participants will be needed. Assuming that 20% of the participants will not be discharged within 12 months and a 25% attrition rate [57], the final number of participants required was estimated to be 624. This calculation was conducted using Stata version 15.

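### The repeated-measures model drops patients with only one follow-up score, although its stated reason, tolerance of missing data, argues for keeping them; bias follows if loss after discharge depends on the discharge score

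*Protocol article*

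**What the plan says.** The Additional objectives section plans "mixed models with repeated measures to explore the impacts of readmission on changes in QoL, empowerment/self-agency-related measure, and self-reported disability". For covariates, "we will adjust for sex, age, diagnosis, baseline score at admission (T1) and present psychiatric status at admission (T1"). The data rule is: "Because the mixed-model method can accommodate missing data, we will use the data from patient-reported measures completed at least twice", and the count is taken "at the three follow-up assessments (T2–T4), in addition to the assessment at admission (T1").

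Three other places bear on it:

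- **Aims and objectives** lists the influence of readmission on change in patient-reported outcomes among the questions the study primarily sets out to answer, although the analysis section calls it additional and exploratory.
- **Primary objectives** keeps any patient who has a T2 QoL score and a known readmission outcome. No later questionnaire is needed.
- **Sample size consideration** allows for "a 25% attrition rate", and Procedures for data collection describes steps against loss at T3 and T4. Some loss after discharge is therefore expected.

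**The concern.** A likelihood-based repeated-measures model gives valid estimates under missing-at-random because each patient contributes whatever was observed, even a single score. Requiring two of three follow-up scores makes entry depend on whether the patient came back. The sentence thus offers the model's tolerance of gaps as the reason for a rule that discards the most telling gap, loss straight after discharge.

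At stake is the change from discharge onward and its difference by readmission. If patients with low scores at discharge are lost more often, those who remain have an inflated T2 mean and the later decline looks too steep. If this happens more among readmitted patients, their T2 deficit shrinks and readmission appears to go with a larger fall than it does.

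**Working it through.** The plan gives no sample size, effect or missingness rate for this model, so there is no figure of its own to reproduce. The check has four steps.

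**1. Who is removed.** Among patients with T1, seven patterns of T2–T4 have at least one score.

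| Pattern | Under the rule |
|---|---|
| T2+T3+T4, T2+T3, T2+T4, T3+T4 | kept |
| T2 only, T3 only, T4 only | dropped |

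One missing follow-up is tolerated. The pattern that matters is T2 only. The T1 condition adds little, because T1 is a covariate and a patient without it would leave the model anyway. A T2-only patient whose readmission status is known enters the primary logistic model, but the same T2 score is discarded here.

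**2. Mechanism.** Let S be the event of having at least two scores and X the model covariates. If P(S | T2, X) varies with T2, then E(T2 | X, S) differs from E(T2 | X) by some shift δ. The T4 mean shifts only by b·δ, where b is the slope of T4 on T2 given T1. Estimated change is therefore off by −(1 − b)·δ. If δ differs by readmission, so does the error, and the readmission contrast moves. If S depends only on X (T1, readmission), δ = 0.

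**3. Size (first simulation).** Assumptions, none from the documents: n = 500, SD 1, all correlations 0.5, readmission effect −0.3 SD at T3 and T4, 200 replicates, unstructured covariance fitted by maximum likelihood, readmission known for everyone. Readmission is set near the protocol's 40% and is somewhat likelier at low T2 scores. Each cell gives complete data / all available scores / two-of-three rule; the Monte Carlo SE of the contrast is 0.006 to 0.008.

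| Loss after T2 depends on | Excluded | Readmission contrast in T2–T4 change | Mean T2–T4 change |
|---|---|---|---|
| nothing | 21% | −0.167 / −0.172 / −0.174 | −0.117 / −0.113 / −0.113 |
| T1 score | 25% | −0.167 / −0.168 / −0.171 | −0.123 / −0.122 / −0.122 |
| T2 score | 24% | −0.172 / −0.172 / −0.180 | −0.124 / −0.123 / −0.199 |
| T2 score and readmission | 24% | −0.170 / −0.166 / −0.212 | −0.119 / −0.120 / −0.225 |
| T2 score, more strongly if readmitted | 23% | −0.172 / −0.173 / −0.312 | −0.117 / −0.115 / −0.197 |

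The target contrast is about −0.17, not −0.3, because readmitted patients already score lower at T2. In the last row the complete-data readmission effect at T4 is −0.365, so the T2 difference is −0.365 + 0.172 = −0.193. With b = (0.5 − 0.25)/(1 − 0.25) = 1/3, the expected T4 effect is −0.3 − 0.193/3 = −0.364, and the contrast is −0.364 + 0.193 = −0.171.

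The mechanism in step 2 accounts for the last row. Under the rule the T4 effect is −0.296, a shift of +0.069, and the contrast shifts by −0.312 + 0.172 = −0.140. The T2 difference has therefore moved by 0.069 + 0.140 = 0.209. One third of that is 0.070 and two thirds is 0.139, as found.

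**4. Second simulation and precision.** Assumptions: 499 patients (624 × 0.80), about 21% lost between T2 and T3, correlation of T1 with later scores 0.4, correlations among T2–T4 0.6. The contrast was −0.196 to −0.200 with all scores. Under the rule it was −0.203, −0.215, −0.248 and −0.290 across four dropout settings, so the largest shift is about 0.09 SD.

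The SE of the T2 readmission difference rose from 0.084 to 0.094–0.097 (0.094/0.084 = 1.12; 0.097/0.084 = 1.15). The objective concerns change, however, and in a further run with the same correlations the SE of the change contrast rose by only 2.5–2.7%.

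**The case against.** The strongest reply is that the model needs each patient's readmission status, and lost patients may not have one. Readmission is recorded on the T3 and T4 staff sheets and drawn from medical records and interviews. Someone who leaves care after discharge may have no known status and then cannot enter under any score-count rule. In the further run, with low scorers lost only among the readmitted:

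| Status known for | All eligible scores | Two-of-three rule |
|---|---|---|
| all lost patients | −0.21 | −0.31 |
| half of them | −0.25 | about −0.31 |
| none of them | −0.31 | −0.31 |

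This stands as a limit on the benefit. Medical records make status plausible for some lost patients, but the documents do not say how many.

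Three further points also stand. The rule keeps patients missing one follow-up, so part of the missing-data handling survives. When loss depends on the T2 score alone, the readmission contrast barely moves (−0.180 against −0.172, about one Monte Carlo SE); only mean change is clearly biased. And the section is headed as additional and exploratory.

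A reader might infer that the rule undoes missing-at-random validity outright, that the planned 25% attrition measures how many patients it removes, or that precision falls by 12–15%. The documents support none of these. Bias needs loss that depends on observed follow-up scores. The 25% inflates the sample for the primary analysis and is not a rate of T2-only patients. The 12–15% belongs to the difference at T2, not to change.

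None of this gives a reason for the rule itself, and the protocol states no offsetting benefit.

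**Conclusion.** The point holds in a conditional form. The rule and its stated reason pull in opposite directions, and the rule selects on later attendance. Whether that does harm depends on facts the documents do not give:

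- Loss completely at random, or dependent only on model covariates: no bias, and a small loss of precision for the change contrast.
- Loss dependent on the T2 score: mean change is biased (−0.199 against −0.124 in the example).
- Loss dependent on the T2 score and on readmission: the readmission contrast is biased as well, by roughly 0.04 SD (−0.212 against −0.170) to 0.14 SD (−0.312 against −0.172). The upper figure needs an assumed score-by-readmission interaction for which the documents offer no evidence.

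With readmission known, using all available scores matched the complete-data result within simulation error in every missing-at-random setting of the first simulation. Correlations, effect and dropout models are assumptions, so these sizes are illustrative. Since the question stands among the study's main aims, the change is worth making, but it does not bear on the primary or secondary logistic results.

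**What to change.** Replace the inclusion sentence so that the repeated-measures models include every discharged participant with a T1 score, known readmission status (taken from medical records where questionnaires are missing) and at least one score at T2–T4, fitted by likelihood or REML under missing-at-random. Keep the two-of-three subset as a sensitivity analysis. Report how many patients have T2 only and, among them, how many have known readmission status, since that number bounds what the change can gain.

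The cost is one sentence in the plan and one extra model run per outcome. No new data are needed beyond the record-based readmission information already planned.
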